### Sample size

RCT power is based on the important biomarker of toxicant exposure, NNAL concentration in urine. Unfortunately, there are no data that reveal the NNK exposure in ECIG users, as that study has not yet been performed. However, we do have data showing how NNAL concentration in novel tobacco product users compares to own brand cigarette use [49]. Using these data, power analysis revealed 100 completers per condition would provide an 80 % power to detect an effect size of 0.28 pmol/ml (SD = 0.6 pmol/ml) on NNAL. We aim to enroll 130 participants per condition anticipating a 20 % attrition rate.

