### Statistical analysis

The analysis plan is based on the primary objective of determining the extent to which ECIG nicotine concentration influences NNK exposure as indexed by urinary NNAL concentration. We will first examine baseline characteristics including demographics and smoking history across study interventions to identify any baseline imbalances after randomization. Discrete variables will be summarized by frequencies and percentages and compared using Chi-squared test or Fisher’s exact test. Continuous covariates will be summarized by mean, standard deviation, median and range, and compared by one-way ANOVA. Skewed continuous variables will be log-transformed or square root transformed as appropriate. We expect groups to be balanced for important baseline characteristics due to randomization. A secondary analysis will be completed adjusting for age, gender, and race, along with any other covariates that differ across research interventions at baseline with a p-value less than 0.20. P-values less than 0.05 will be considered statistically significant with the exception of analysis of our primary analysis, where p-values less than 0.008 will be considered significant after a Bonferroni multiple comparisons adjustment. Our primary endpoint, urine NNAL concentration, will be summarized by study intervention and time and analyzed using linear regression, and we will adjust the Type I error rate to account for 6 pairwise comparisons at each time point. We will compare each ECIG group to the cigarette substitute and then each ECIG group to the other. An analogous approach will be used to analyze our secondary endpoints. The primary analysis of our secondary endpoints will use linear regression. Secondary analyses will consist of an adjusted analysis and a repeated measures analysis using a linear mixed model. All analysis will be completed using SAS (v.9.4) under the expertise of a senior biostatistician.

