In terms of control condition selection, the use of both an ECIG containing 0 mg/ml in addition to a control condition where no ECIG aerosol or nicotine is delivered (cigarette substitute) also is an important strength of the current design. Importantly, as this RCT is not a smoking cessation treatment study and we are not recruiting individuals interested in smoking cessation, the treatment-related equipoise considerations required of most RCTs are less applicable here. We see the cigarette substitute condition as a vital comparator to understand how ECIG aerosol and ECIG-delivered nicotine may affect user health among our other primary aims. While we anticipate the possibility that those assigned to the cigarette substitute condition could be more likely to withdraw their participation, Visit 10 procedures (ECIG provision to individuals who were randomized to the cigarette substitute) are intended to reduce this likelihood following the intervention period.

Another factor that needed to be considered when designing this protocol was the evaluation of side effects that ECIG users may experience. While the previous RCT trials highlighted potential adverse effect profiles of ECIG use, the RCT described here will also assess less well-known side effects related to ECIGs using results from recent qualitative work [43]. Learning from mixed design studies assessing potential adverse effects associated with ECIG use ensures that we are examining and characterizing both common and uncommon side effects related to ECIG use throughout the intervention and follow-up periods.

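### The primary NNAL analysis is a separate regression at each visit and the mixed model is only secondary, although the plan foresees 20% attrition and possibly heavier withdrawal from the comparator arm

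*Protocol article*

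**What the plan says.** Under Statistical analysis, the protocol article fixes the primary method: "Our primary endpoint, urine NNAL concentration, will be summarized by study intervention and time and analyzed using linear regression". Testing is done visit by visit: "we will adjust the Type I error rate to account for 6 pairwise comparisons at each time point", with the threshold that "p-values less than 0.008 will be considered significant after a Bonferroni multiple comparisons adjustment".

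The longitudinal model comes later in the same section: "Secondary analyses will consist of an adjusted analysis and a repeated measures analysis using a linear mixed model". The sentence just before it concerns other endpoints: "The primary analysis of our secondary endpoints will use linear regression". It is therefore unclear whether the mixed model is planned for NNAL at all. Adjustment for covariates is also described as a secondary analysis, and baseline NNAL is not among the covariates named.

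Under Sample size, the calculation is in completers ("100 completers per condition would provide an 80 % power to detect an effect size of 0.28 pmol/ml (SD = 0.6 pmol/ml) on NNAL") and one attrition rate is given for all arms: "We aim to enroll 130 participants per condition anticipating a 20 % attrition rate". Withdrawal criteria states that participants who remove themselves are not contacted again. Blinding states that assignment to the cigarette substitute is open. The Discussion raises, as a possibility only, that "those assigned to the cigarette substitute condition could be more likely to withdraw their participation". The countermeasure is a product offer at Visit 10 (week 24), made known at consent.

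Study visits places urine collection at weeks 0, 4, 12 and 24.

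**The concern.** A regression fitted to the NNAL values of one visit uses only participants measured at that visit, unless missing values are filled in. Someone who gave urine at weeks 0, 4 and 12 and then left adds nothing to the week-24 comparison.

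This matters for the contrast between arms when two things happen together: drop-out differs between arms, and those who leave have different NNAL from those who stay. If participants who cut down least leave the substitute arm more often, those remaining look better than the arm as randomised, and the ECIG-versus-substitute differences shrink. The first aim states its NNAL hypothesis relative to that arm, and three of the six primary comparisons use it as reference. The three comparisons among ECIG arms are less exposed, because those arms are blinded to nicotine concentration and the plan suggests no uneven withdrawal among them.

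The trial already plans a model that uses the earlier values and allows drop-out to depend on them. The concern is its ranking, and possibly its scope.

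**Working it through.** **The plan's own figures.** Inputs from Sample size: difference 0.28 pmol/ml, SD 0.6, 100 completers per arm, 130 enrolled per arm, 20% attrition.

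- Enrolment: 100/(1 - 0.20) = 125, so 130 is enough; 130 x 0.80 = 104 completers per arm. Over the trial, 520 x 0.20 = 104 participants would be lost. The plan does not date the attrition and follow-up runs to week 36, so 104 is an upper figure for week 24 at that rate.
- Power: the standardised difference is 0.28/(0.6 x sqrt(2/100)) = 3.30. Normal-approximation power is 91.0% at two-sided 0.05, 74.1% at two-sided 0.008, and about 81.7% at two-sided 0.05/3 or one-sided 0.05/6. The stated 80% is reproduced only by the last two. That is a separate matter; here the calculation serves to confirm the 0.28 and 0.6 used below.

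**Algebra of the bias.** Let p be an arm's drop-out proportion and g the mean NNAL of drop-outs minus that of completers. Then the mean of all = mean of completers + p x g. If g is the same in both arms, the bias of the completer contrast has size (p_sub - p_ECIG) x g. It is zero when the two rates are equal, even if drop-out depends on NNAL, and zero when g = 0.

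The plan gives no rates by arm and no g. Two assumed splits keep 20% overall: (0.30 + 3 x 0.1667)/4 = 0.20 and (0.40 + 3 x 0.1333)/4 = 0.20. With g = 0.15, 0.30 and 0.60 pmol/ml (0.25, 0.5 and 1 SD):

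- 30% versus 16.7%: 0.1333 x g = 0.02, 0.04, 0.08
- 40% versus 13.3%: 0.2667 x g = 0.04, 0.08, 0.16

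**Simulation.** Assumptions, none of them in the document: visits at weeks 0, 4, 12 and 24; 130 per arm; SD 0.6; equal correlation between visits of 0.5 or 0.7; a true difference of 0.28 reached by week 12 (half at week 4); permanent drop-out with log-odds rising 0.5 or 1.0 per SD of the last observed NNAL; 1,500 runs per setting. Monte Carlo error is about 0.08/sqrt(1500) = 0.002. Entries are bias at week 24 in pmol/ml; positive means toward no effect.

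| Drop-out, substitute / ECIG | Correlation | Slope | Completers, unadjusted | Completers, baseline-adjusted | Likelihood, all visits |
|---|---|---|---|---|---|
| 20% / 20% | 0.5-0.7 | 0.5-1.0 | -0.003 to 0.002 | -0.002 to 0.003 | -0.003 to 0.001 |
| 30% / 16.7% | 0.5 | 0.5 | 0.025 | 0.009 | 0.002 |
| 30% / 16.7% | 0.5 | 1.0 | 0.038 | 0.015 | -0.001 |
| 30% / 16.7% | 0.7 | 0.5 | 0.029 | 0.007 | -0.002 |
| 30% / 16.7% | 0.7 | 1.0 | 0.056 | 0.014 | 0.000 |
| 40% / 13.3% | 0.5 | 0.5 | 0.053 | 0.020 | 0.005 |
| 40% / 13.3% | 0.5 | 1.0 | 0.080 | 0.031 | 0.001 |
| 40% / 13.3% | 0.7 | 0.5 | 0.065 | 0.013 | -0.001 |
| 40% / 13.3% | 0.7 | 1.0 | 0.107 | 0.025 | -0.003 |

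A simpler simulation, with drop-out driven by week-4 NNAL alone and the same correlations and slopes, gave completer bias of 0.016-0.043 and 0.035-0.088 for the two splits.

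Taking both simulations together:

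- 30% versus 16.7%: 0.016 to 0.056. 0.016/0.28 = 6% and 0.056/0.28 = 20%.
- 40% versus 13.3%: 0.035 to 0.107. 0.035/0.28 = 13% and 0.107/0.28 = 38%.

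**Precision.** The likelihood analysis lowered the standard error against the unadjusted completer regression by at most about 7% (0.0873 to 0.0816), and in one setting it was 2% higher (0.0820 to 0.0836). It was fitted separately by arm, without baseline adjustment between arms, so these figures do not describe a model with baseline NNAL as covariate.

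**The case against.** - **The plan does not forecast uneven attrition.** A reader might infer that heavier loss from the substitute arm is expected. The Discussion raises it only as a possibility, and Sample size gives a single 20% with no split by arm. With equal drop-out the simulated bias is about zero. This stands, and the point is conditional on it.
- **Per-visit regression is not invalid merely because drop-out is related to NNAL.** The algebra shows that a contrast can be unbiased when rates and gaps are equal across arms. This stands too.
- **The reason the plan suggests for leaving is not NNAL.** Study visits describes people who joined hoping for an ECIG and were assigned the substitute. If such disappointment is unrelated to NNAL, there is no bias. If it leads to exit before week 4, those participants have at most a baseline value, and the mixed model gains little for them. This narrows the benefit without removing it: participants who reduce less may also leave later, after giving urine.
- **Using only those who remain is an inference.** The article does not say how missing NNAL enters the regression, and an analysis plan that is not shown may add imputation. Completers is a sample-size term here, not a declared analysis set. The absence of missing-data detail is therefore no finding. The ranking of the two analyses, however, is stated in the article.
- **Baseline adjustment may be enough.** Adding baseline NNAL to the regression cut the simulated bias to 0.007-0.031 under uneven drop-out. That is a real improvement, but the primary regression as described does not include it, and some bias remains.

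**Conclusion.** The concern holds in a conditional form. The article ranks a per-visit regression above a repeated-measures model that would use the week 0, 4 and 12 values of participants who leave, while naming the circumstance in which that ranking could distort its substitute contrasts. If the mixed model is meant only for secondary endpoints, NNAL has no longitudinal analysis in the article and the point is stronger.

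Under the stated assumptions, bias toward no effect is about 0.02-0.06 pmol/ml (6-20% of 0.28) at 30% versus 16.7% drop-out, and 0.04-0.11 (13-38%) at 40% versus 13.3%, against 0.005 or less for the likelihood analysis under missing at random. The direction depends on higher-NNAL participants being the ones who leave. The scale is pmol/ml as in Sample size; a log transformation would change the units.

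A loss of more than half the planning effect (0.16/0.28 = 57%) might be inferred from the simple formula. It needs 40% substitute drop-out together with a 1 SD gap; neither is in the document, and it lies outside the simulated range. The change is worth making because it is cheap, not because bias has been shown.

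**What to change.** Make the repeated-measures linear mixed model the primary NNAL analysis, on all randomised participants as assigned. Include arm, visit, arm-by-visit, baseline NNAL, baseline-by-visit and site, with unstructured covariance. Test the arm contrasts at one visit named in advance, for example week 24, the end of the intervention. State explicitly that the model applies to NNAL. Keep the per-visit regression as a sensitivity analysis. If the sponsor prefers the present ranking, justify it.

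The cost is analysis wording: no new data or visits are needed, and a mixed model is already planned. The limits should be stated with it. The model relies on missing at random, so drop-out that depends on unobserved NNAL still needs sensitivity analysis. Participants who leave before week 4 contribute little, and nothing to the contrast if baseline enters only as a covariate. Little precision should be expected from the extra visits (about 0-7%); the gain is in bias.

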### Ethical considerations

Ethics approval was granted from the VCU and PSU Institutional Review Boards (VCU IRB: HM20002759; PSU IRB: STUDY00001095). Verbal consent will be obtained at the time of first contact over the telephone with the research team, and written consent will be obtained when participants attend their first study visit. All data will be entered, stored and backed-up in a secure manner via the REDCap database system.

## Discussion

This RCT uses a two-site, four-arm, 6-month, parallel-group design with a follow-up to 9 months. Participants are randomized to one of four conditions: a cigarette substitute negative control, or one of three ECIG conditions that differ by nicotine concentration 0, 8, or 36 mg/ml. The primary aims of this study are to characterize ECIG influence on toxicants, biomarkers, health indicators, and disease risk; determine tobacco abstinence symptom and adverse event profile associated with real-world ECIG use; and examine the influence of ECIG use on conventional tobacco product use. Liquid nicotine concentration-related differences on these study outcomes are predicted. These aims will address gaps identified by several reviews of ECIG-associated literature [3, 22, 51] and were chosen specifically for their relevance to proximal health effects as well as longer term health outcomes.

There were many factors considered during development of the current protocol. The two previous ECIG RCTs performed [16, 17] were important in that they demonstrated the challenges of ECIG product and control group selection. In response to this challenge, analytical and clinical laboratory testing were used to understand relevant ECIG device characteristics and nicotine delivery profile of the ECIG liquid nicotine concentrations chosen. The external analytic confirmation of nicotine content in all ECIG liquid used in the current RCT is also an important design characteristic and is in contrast to most clinical examinations of ECIG use [16, 17]. Prior knowledge of the liquid nicotine content and nicotine delivery capabilities of the device/liquid combination will strengthen the results obtained. Additionally, research staff at each site are responsible for filling individual cartomizers for this RCT. While more labor intensive, this procedural design detail allows for complete control and responsibility to ensure the integrity of liquid nicotine concentration in each participant’s cartomizers. As previously noted, we will test the liquid to confirm the nicotine concentration for additional safeguarding. We considered purchasing pre-loaded cartomizers, but decided the labor intensive approach was more appropriate given the importance of this element of the RCT.

In terms of control condition selection, the use of both an ECIG containing 0 mg/ml in addition to a control condition where no ECIG aerosol or nicotine is delivered (cigarette substitute) also is an important strength of the current design. Importantly, as this RCT is not a smoking cessation treatment study and we are not recruiting individuals interested in smoking cessation, the treatment-related equipoise considerations required of most RCTs are less applicable here. We see the cigarette substitute condition as a vital comparator to understand how ECIG aerosol and ECIG-delivered nicotine may affect user health among our other primary aims. While we anticipate the possibility that those assigned to the cigarette substitute condition could be more likely to withdraw their participation, Visit 10 procedures (ECIG provision to individuals who were randomized to the cigarette substitute) are intended to reduce this likelihood following the intervention period.

Another factor that needed to be considered when designing this protocol was the evaluation of side effects that ECIG users may experience. While the previous RCT trials highlighted potential adverse effect profiles of ECIG use, the RCT described here will also assess less well-known side effects related to ECIGs using results from recent qualitative work [43]. Learning from mixed design studies assessing potential adverse effects associated with ECIG use ensures that we are examining and characterizing both common and uncommon side effects related to ECIG use throughout the intervention and follow-up periods.

While there are a number of strengths regarding this RCT design, there have also been barriers to success that were faced during preliminary stages. In particular, there is not a universally agreed upon definition of an ECIG “use” within the literature and scientific community at this time. There are a number of mechanisms that can be used to measure cigarette and product use, such as daily text messages or the use of interactive voice response technologies. Daily diaries were chosen for this RCT due to the length of the intervention period and its complexity. In addition, the ECIG batteries included an automated puff counters on the ECIG which allowed for greater accuracy of use measurement. A related design challenge was the assessment of other tobacco product use and measures to assess ECIG use. There are few standardized measures of ECIG use [52], thus assessments for both during the intervention and follow-up phase needed to be developed and adapted from other sources. Future ECIG evaluations should consider these design aspects, specifically controlling the ECIG liquid used as well as the filling of cartomizers to ensure quality control.

Finally, this RCT design can inform the United States Food and Drug Administration’s (FDA) Center for Tobacco Products regulation standards for ECIGs and other tobacco products where cessation is not an indication (i.e., cessation is covered by FDA Center for Drug Evaluation and Research). The act giving the FDA its authority over tobacco products makes clear that regulation should be based on verifiable, scientific evidence. This science-based regulation involves evaluating the health effects of a potential tobacco product, especially the effects that might be expected under real-world use conditions. However, there are few demonstrated methods for predicting effects in the real world. This issue is becoming more critical as novel tobacco products are proliferating and evolving and major tobacco companies are revealing the pivotal role that novel tobacco products such as ECIGs play in their future business endeavors. ECIGs represent an important product category to examine and results from this study will inform knowledge concerning their use as well as demonstrate how this model may be applied to other tobacco products.

## Abbreviations

CO: Carbon monoxide
ECIG: Electronic cigarette
NNAL: 4-(methylnitrosamino)-1-(3-pyridyl)-1-butanol
NNK: 4-(methylnitrosamino)-1-(3-pyridyl)-1-butanone
TLFB: Timeline follow back
